### Assessment

#### Measurement of extra therapy time

The difference between the intervention and the control nursing homes is the input of nurses resulting in extra exercises. In this way patients can increase their time spent on therapeutic activities. This is measured by Behavioural Mapping method [10,14,15]. Behavioural Mapping is a time sampling technique that provides registration of systematic and accurate observations resulting in therapeutic activities, nontherapeutic activities, interaction with others, and locations where activities take place. Observation of patients take place at 10- minutes intervals on weekdays (8:30–17:10). At each time point the observer records patient activity, the person attending to the patient and the patient’s location. In accordance to other studies the assumption is made that between two consecutive observations the three observation domains remain unchanged [10-15].

### Outcome measures

#### Patient characteristics

The following background characteristics are measured in both patient groups: age, gender, level of education, marital status, living situation, smoking and drinking alcohol.

### Medical history data

Type of stroke, TIA, Parkinson, disorders of consciousness, brain tumor, epilepsy, alcohol or other abuse, depression and or psychiatric problems and medication. Medication use is coded according to the guideline of the Dutch Pharmacotherapeutic Compass [36].

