**Methods:**

A comparative single blind controlled study will be applied. Patients suffering from a stroke and staying on one of the rehabilitation units of the nursing homes are eligible for participation. Participants belong to the intervention group if they stay in two nursing homes where four interventions of the Clinical Nursing Rehabilitation Stroke Guideline were implemented. Participants who stay in two nursing homes where therapy is given according to the Dutch stroke Guideline, are included in the control group. Clinical neuropsychologists will assess patients’ cognitive functioning, level of depression (mood) and anxiety. Nurses will assess a Barthel Index score on a weekly basis (ADL). These variables are measured at baseline, after 8 weeks and at the moment when participants are discharged from the nursing home.

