### Study population

Patients suffering from a stroke will be eligible for participation, even if they suffer from co-morbid diseases such as heart disease, recurrent stroke or pre-existing depression. Patients will be excluded if they will leave the rehabilitation unit within two weeks, when they are too ill to participate, if there is a language problem, like aphasia, or when a Mini-Mental State Examination (MMSE) [35] score is lower than 13. A score of 13 or higher is a prerequisite for a neuropsychological assessment. Patients will be recruited by the head of the nursing staff, working on the rehabilitation unit of the nursing homes. Oral and written information about the study is given to the patients and/or their legal representatives. Prior to their participation in the study oral and written informed consent will be acquired from all the participants, their family or legal representatives. Informed consent will be based on veracity, anonymity, privacy, and confidentiality.

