### Procedure

Within the first week of stay at the stroke units, eligible patients are tested by clinical neuropsychologists. They assess patient’s cognition and mood. These variables are measured at baseline, after 8 weeks and at discharge from the nursing home where the patient rehabilitates. In practice the moment of discharge can vary depending on the patient’s condition and personal situation. Therefore when patients are discharged earlier than 8 weeks the moment of discharge is selected as post measurement.

Nursing staff collects patients background characteristics at entry of the study and assesses a Barthel Index score every week. A geriatric physician collects medical history data.

The control group receives exercise therapy provided by physiotherapists or occupational therapists, once a day during 30 minutes on weekdays, but not in weekends. The intervention group receives the same therapy as the control group. Additionally, patients in the intervention group are stimulated, helped and controlled by nurses to carry out exercises from their exercise map every day including weekends. This results in approximately 10 to 20 extra exercise moments a day for these patients.

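### Follow-up runs from nursing-home admission and no stroke date is listed, so a difference between homes in time since stroke could pass for a therapy effect

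*Protocol article*

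**What the plan says.** - **Clock.** The Procedure section starts the assessments at admission: "Within the first week of stay at the stroke units, eligible patients are tested by clinical neuropsychologists". For later tests it states: "These variables are measured at baseline, after 8 weeks and at discharge from the nursing home where the patient rehabilitates". For shorter stays it adds: "Therefore when patients are discharged earlier than 8 weeks the moment of discharge is selected as post measurement". No assessment is timed from stroke onset.
- **Eligibility.** The Study population section is broad: "Patients suffering from a stroke will be eligible for participation, even if they suffer from co-morbid diseases", with recurrent stroke among its examples. It sets no minimum or maximum time since stroke.
- **Data collected.** Patient characteristics lists "age, gender, level of education, marital status, living situation, smoking and drinking alcohol". Medical history data lists "Type of stroke, TIA, Parkinson, disorders of consciousness, brain tumor, epilepsy, alcohol or other abuse, depression and or psychiatric problems and medication". Stroke type is there; stroke date and time since stroke are not.
- **Allocation.** The abstract defines the arms by place of stay: "Participants belong to the intervention group if they stay in two nursing homes where four interventions of the Clinical Nursing Rehabilitation Stroke Guideline were implemented". The controls come from two other homes, and the Randomisation section describes a convenience sample.
- **Analysis.** The Data-analysis section plans descriptive statistics, a t-test for baseline comparability, and a repeated-measures MANOVA over the three test moments. It names no covariate.

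**The concern.** Stroke patients improve without extra therapy, and the improvement slows with time. Two patients admitted at different intervals after their strokes are therefore expected to change by different amounts over the same 8 weeks, even under identical care. Randomisation would balance that interval on average. Allocation by home does not, because the interval may depend on where a home's patients come from and how soon they are transferred.

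The effect of interest is a difference between arms in change over time, which is also the pattern that unequal intervals would leave. With no stroke date among the listed variables and no covariate in the model, the analysis as written could neither show such an imbalance nor adjust for it. What is at stake is the attribution of a group-by-time difference to therapy time. The direction of any bias is unknown: it favours whichever arm is admitted earlier after stroke.

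**Working it through.** **Inputs from the article (Sample size section).** Planned effect d = 0.30; 69 patients per group before dropout. Both are taken as stated, and the point does not depend on how they were derived. The article gives no recovery curve and no stroke-to-admission interval, so there is no figure of its own to reproduce here.

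**Assumed inputs.** Recovery since stroke R(t) = A × (1 − exp(−t/τ)), with A = 0.5 to 1.5 SD and τ = 4 to 10 weeks. Mean interval from stroke to admission 2 to 5 weeks, differing by 1 or 2 weeks between arms. No treatment effect.

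**Step 1: spurious difference in 8-week change.** A patient admitted t0 weeks after stroke gains

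A × exp(−t0/τ) × (1 − exp(−8/τ)).

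For A = 1 and τ = 6, 1 − exp(−8/6) = 0.736. Then t0 = 2 gives 0.528 and t0 = 4 gives 0.378, a difference of 0.15 SD, half of d = 0.30. Other combinations:

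| A (SD) | τ (weeks) | Intervals (weeks) | Difference in change (SD) |
|---|---|---|---|
| 0.5 | 10 | 3 v 4 | 0.019 |
| 0.5 | 6 | 2 v 3 | 0.04 |
| 1.0 | 6 | 3 v 4 | 0.069 |
| 1.0 | 6 | 2 v 4 | 0.15 |
| 1.5 | 6 | 2 v 4 | 0.224 |
| 1.5 | 4 | 2 v 4 | 0.31 |

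With equal intervals the difference is zero for every A and τ.

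**Step 2: effect on the type I error.** As a stand-in for the MANOVA, take a two-sided 5% z-test on change, 69 per arm, with correlation r between the two time points: SE = √(2(1 − r)) × √(2/69). For r = 0.5 the SE is 0.170 SD; for r = 0.7 it is 0.132 SD.

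| Spurious difference (SD) | False-positive rate, r = 0.5 to 0.7 |
|---|---|
| 0.04 | about 6% |
| 0.10 | 9 to 12% |
| 0.15 | 14 to 21% |
| 0.20 | 22 to 33% |
| 0.30 | 42 to 62% |

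**Step 3: would the baseline check show it?** If both arms follow the same curve, unequal intervals also separate the baseline scores. For A = 1, τ = 6 and intervals of 2 and 4 weeks, recovery at baseline is 1 − exp(−2/6) = 0.283 and 1 − exp(−4/6) = 0.487, a gap of 0.20 SD. With τ = 6 the gap in change is always 0.736 of the baseline gap, so the baseline scores do carry a signal. But 0.20 × √(69/2) = 1.17, and 1.17 − 1.96 = −0.79, so the power of a two-sided test is about 22%. If the arms also differ in severity or in potential for recovery, baseline scores can agree while the intervals differ. The check is weak, not empty.

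**Limit.** Steps 1 and 2 cover change at 8 weeks only. The primary goal in the Background concerns cognition at discharge, whose timing varies, so these figures do not describe that endpoint.

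**The case against.** **The article condenses a fuller protocol.** A stroke date is the kind of field that a data-collection form may hold without an article mentioning it, and the medical-history sentence does not claim to be exhaustive. This stands in part: the date may be collected. However, the two sections are itemised, down to marital status and smoking, and the point does not rest on the missing field alone. The admission-based clock, the open eligibility, the allocation by home and a model without covariates are all fixed in the article.

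**Selection bias is already acknowledged.** The Discussion names it as a possible result of the convenience sample. It does not mention time since stroke and offers no remedy, so the caveat does not answer the point.

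**There is no evidence that the homes differ.** This stands. A reader might infer that the design will produce a spurious effect. The article describes neither referral patterns nor intervals, so it supports only that the design could.

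**The baseline check may catch it.** A reader might infer that the t-test can reveal nothing. That is too strong: the comparability check is not confined to test scores, and under a common recovery curve baseline scores would differ too. It remains true that the check can cover only recorded variables and has little power at this sample size.

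**The gap can be repaired.** A reader might also infer that the imbalance could never be examined afterwards. That holds only for the listed data; the date may be retrievable from records.

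**Conclusion.** The concern holds as a conditional one. If time from stroke to admission differs between the intervention and control homes, the planned analysis could credit natural recovery to therapy time, and the listed data would give little warning.

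Its size is not known. Under a decelerating recovery of 0.5 to 1.5 SD, a time constant of 4 to 10 weeks and a 1 to 2 week difference in interval, the spurious difference at 8 weeks is roughly 0.02 to 0.31 SD, from negligible to about the planned effect of 0.30. All of these inputs are assumptions.

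This is a material and cheaply reduced threat to the primary inference, worth acting on. It does not show that the trial is invalid. Nor would adjustment settle the matter: a reader might infer that an effect which survives it can be attributed to therapy time, but with two homes against two, other differences between homes would remain.

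**What to change.** 1. Add the date of the qualifying stroke, and whether it is a first or recurrent stroke, to the Medical history data list. Retrieve both from records for patients already enrolled. If a fuller form already holds them, say so.
2. Report days from stroke to baseline by arm and by home.
3. Prespecify that interval and its interaction with time as a covariate in the effect model.
4. State that this reduces but does not remove confounding by home, and that the interval may be partly collinear with home, so its contribution may be hard to separate. Set no rule that an effect surviving the adjustment may be attributed to therapy time.

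Cost: one extra data field group, collected by the geriatric physician who already takes the history, and one extra covariate with its interaction. No treatment, visit or outcome changes.

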### Effect evaluation

#### Primary outcome measures cognition

##### Assessment of cognition

Cognition will be assessed by the following neuropsychological tests:

### Global cognitive functioning

#### Mini-mental state examination

Global cognitive functioning will be assessed by the Mini-Mental State Examination (MMSE). MMSE is a brief screening test and has been developed to screen for cognitive impairment, which has a joint reliability of 0.95 in a study of patients with various neurological disorders [35].

### Executive functions

#### Behavioural assessment of dysexecutive syndrome

##### Rule Shift Cards

A subtest of the BADS [37] is the Rule Shift Cards (BADS-RS), which is meant to assess set-shifting. This subtest discriminates people with an executive dysfunction from healthy people. Participants have to respond to stimuli (red or black playing cards) according to two rules that are presented consecutively. The maximum score is 4.

##### *Key-search test*

Another subtest of the BADS is the Key-search test. This test assesses the executive sub functions planning and problem-solving. The goal is to choose a systematic, and efficient strategy to find a key lost in a field. The inter-rate reliability of the BADS varies from 0.88-1.00. Brain injured patient achieve significant lower scores on the test which suggest that construct validity of these tests is as good as that of established tests [37]. The maximum score is 4.

#### Category fluency

Set-shifting, one of the executive functions, will be assessed by Category Fluency [38,39]. This test requires shifting from one category of names to another category. This test uses the category ‘animals’, test re-test reliability 0.82, and professions, test re-test reliability 0.96.

### Verbal and non-verbal memory

#### ‘Eight words test’

The patient is asked to memorize 8 words which have to be reproduced by the participant in different settings at 5 consecutive times with different time delays [40]. The maximum score of the Eight words test is 40.

#### Rivermead behavioural memory test

Episodic memory will be tested by the Rivermead Behavioural Memory Test (RBMT) Face and Picture Recognition [41]. The Face Recognition subtest is meant to assess nonverbal episodic memory; the Picture Recognition subtest is meant to assess both verbal and nonverbal episodic memory. The RBMT has reliability coefficients ranging from 0.57 to 0.86, with the inter scorer reliability of the RBMT being 0.9 or higher. The maximum score of the Face Recognition subtest is 10. The maximum score of the Picture Recognition subtest is 20 [41].

### Executive functions combined with memory

#### Montreal cognitive assessment

Montreal Cognitive Assessment (MOCA) assesses executive functions, attention and concentration, memory, language, orientation, calculation, conceptual thinking, and visuoconstructional skills [42]. The MOCA detects mild cognitive impairment with 90%-96% sensitivity and 87% specifity [42].

### Secondary outcome measure

#### Mood

The level of depression and anxiety will be assessed by the following questionnaires:

#### Beck depression inventory (BDI)

The BDI is a 20-item questionnaire used to measure the level of depression, with a high reliability (Coefficient Alpha = .86) [43]. A low score indicates a low level of depression [43]. The maximum score of the BDI is 60.

#### Symptoms checklist 90 (SCL90)

This test is a short test to examine anxiety and depression [44]. The scale exists of 25 questions about anxiety and depression, with an internal consistency coefficient rating range of .79 for paranoid ideation to .90 for depression. A higher score indicates a higher level of depression and anxiety. The maximum score of the SCL90 is 125 [44].

### Activities of daily life

Activities of daily life are measured by the Barthel Index [45].

#### Barthel index

The Barthel Index consists of 10 items, all focused on ADL activities. The total score of the Barthel Index ranges between 0 and 20 points. The Barthel Index has a high level of reliability and validity in patients with stroke [45].

### Intervention

#### Additional clinical nursing rehabilitation stroke guideline

##### Control group

Patients in the control nursing homes, receive approximately four hours a week of traditional rehabilitation based on the Dutch Stroke Guideline [17].

##### Experimental group

During their stay, patients in the intervention group, get extra therapy based on the Clinical Nursing Rehabilitation Stroke Guideline: muscle strengthening, sitting balance and reach, getting up from a chair and walking [34]. Nurses perform all exercises during the daily activities of the patients, including weekends, resulting in an extra therapy time of approximately five hours a week compared to the control group. These exercises are adapted to the patient‘s individual goals, need and rehabilitation level by physiotherapists and occupational therapist in consultation with the responsible nurses. Exercises will be documented in an exercise map which is fixed to the bed or wheelchair of the patient. Nurses coordinate the weekly adjustment exercises by informing the multidisciplinary team about the patient’s progress.

### Procedure

Within the first week of stay at the stroke units, eligible patients are tested by clinical neuropsychologists. They assess patient’s cognition and mood. These variables are measured at baseline, after 8 weeks and at discharge from the nursing home where the patient rehabilitates. In practice the moment of discharge can vary depending on the patient’s condition and personal situation. Therefore when patients are discharged earlier than 8 weeks the moment of discharge is selected as post measurement.

Nursing staff collects patients background characteristics at entry of the study and assesses a Barthel Index score every week. A geriatric physician collects medical history data.

The control group receives exercise therapy provided by physiotherapists or occupational therapists, once a day during 30 minutes on weekdays, but not in weekends. The intervention group receives the same therapy as the control group. Additionally, patients in the intervention group are stimulated, helped and controlled by nurses to carry out exercises from their exercise map every day including weekends. This results in approximately 10 to 20 extra exercise moments a day for these patients.

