### Sample size

The sample size has been calculated by using the statistically power analysis program G Power. The estimated effect-size comes from a study reporting the effect of physical activity on cognition in patients with stroke (*d’* = 0.30) [27]. Taking into account a type one error of 0.05 (α = 0.05), a power of 0.80 (β = 0.08), three repeated measurements and two groups, a sample size of 138 patients is required, i.e. 69 persons in each group. Taken a dropout of 10% into account, a sample size of 81 persons in each group is required.

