### Data-analysis

Descriptive analysis on all the patient characteristics at baseline is performed. A t-test for independent groups will be used to check for comparability between the intervention and control group at baseline. A repeated-measures multivariate analysis of variance (MANOVA) will be applied to assess possible effect of increased therapeutic time over various test moments (baseline, 8 weeks and at the moment of discharge). The level of significance is 0.05. The SPSS-PC version no. 20 will be used for data-analyses (SPSS Inc., Chicago, IL, USA).

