## Discussion

The present protocol paper describes the design of a single blind controlled trial. The aim of our study is to investigate whether additional therapy time focused on muscle strengthening, sitting balance and reach, getting up from a chair and walking has a positive effect on cognition, mood and activities of daily living (ADL) in stroke patients who rehabilitate on rehabilitation units of nursing homes. The study gives insight into how the care of elderly stroke patients in nursing homes might be improved so that patients have a better chance of independent living. When positive effects will be found this study can guide policy makers and practitioners on how to implement higher quality care on rehabilitation wards of nursing homes.

The strength of the study is that 1) interventions from the evidence based Clinical Nursing Rehabilitation Stroke Guideline are implemented in the rehabilitation care of older stroke patients. This implementation will significantly increase the time spent on therapeutic activities without extra therapists needed, 2) the role of nurses can shift towards a more therapeutic one, 3) we examine if an increase in therapeutic time has a beneficial effect on cognition, mood, and ADL. These factors are of great importance for rehabilitation success in stroke patients. Possible limitations of our study are 1) the high rate of drop-out due to illness or death of this frail patient group, 2) the convenience sample causing a possible selection bias, 3) the limited intervention time before patients are discharged from the rehabilitation units.

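### Patients discharged before 8 weeks have two assessments, but the analysis is a three-occasion repeated-measures MANOVA, so they are deleted or their scores misplaced

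*Protocol article*

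**What the plan says.** The Procedure section sets the assessment schedule for cognition and mood: "These variables are measured at baseline, after 8 weeks and at discharge from the nursing home where the patient rehabilitates". It then allows for variable stays: "In practice the moment of discharge can vary depending on the patient’s condition and personal situation". The rule that follows is: "Therefore when patients are discharged earlier than 8 weeks the moment of discharge is selected as post measurement".

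The Data-analysis section names one effect analysis: "A repeated-measures multivariate analysis of variance (MANOVA) will be applied to assess possible effect of increased therapeutic time over various test moments". It lists those moments as baseline, 8 weeks and discharge. The Sample size section rests its 138 patients (69 per group) on "three repeated measurements and two groups", and raises this to 81 per group for 10% dropout.

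Three other statements bear on the point. The Study population section excludes on length of stay only those due to leave within two weeks. The Background places the primary goal, cognition, at discharge. The Study design section allocates by nursing home: two intervention homes and two control homes.

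**The concern.** A patient who goes home at week 4 is eligible and is assessed at baseline and at discharge. There is no separate 8-week assessment. The planned model has three cells per patient, and the article does not say what goes in the third. This is a conflict between two rules that the article does state, so it is more than detail left to an analysis plan.

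Timing adds to it. Patients who stay 8 weeks or longer have a post measurement at a fixed time. For early leavers, the score that stands in for it comes at whatever time they leave. The discharge occasion varies in time for everyone. The MANOVA treats each occasion as the same moment for all patients and does not use elapsed time.

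Two things are at stake. If early leavers are deleted, the trial loses patients according to something related to outcome, and loses power. If their scores are placed or repeated, the arms may be compared after different amounts of recovery whenever length of stay differs between them. That difference could come from the intervention, or from discharge practice in the homes, since each home belongs wholly to one arm.

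**Working it through.** **1. Occasions available against occasions required**

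| Stay | Distinct assessments | Cells in the model |
|---|---|---|
| Beyond 8 weeks | baseline, 8 weeks, discharge (3) | 3 |
| 2 to 8 weeks | baseline, discharge (2) | 3 |

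For the second row there are three possibilities: the patient lacks a value and is dropped listwise; the discharge score goes into the 8-week cell and the discharge cell is empty, so the patient is dropped anyway; or the discharge score fills both cells, so an earlier week counts as week 8 and change between the last two occasions is zero by construction. The article does not choose.

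**2. The plan's own sample size**

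The figure of 138 cannot be reproduced uniquely, because the correlation between occasions, the effect tested and the sidedness are not given. Taking d = 0.30 as f = 0.15, with two groups, three occasions and correlation 0.5, 80% power needs 236 patients in total for the between-group effect, 74 for the group-by-time effect (univariate) or 76 (MANOVA). A total near 138 needs a correlation close to 0. The steps below therefore take 80% power at 69 per arm at face value. Also, 69 / 0.9 = 76.7, so 77 per arm would cover 10% dropout. The planned 81 leaves 81 × 0.9 = 72.9, a small reserve.

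**3. Loss under listwise deletion**

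Let p be the share discharged before 8 weeks. It is not in the document, so a range is assumed.

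- Patients per arm with three occasions: n = 81 × 0.9 × (1 − p)
- Power = Φ(2.80 × √(n / 69) − 1.96), where 2.80 = 1.96 + 0.84 gives 80% at n = 69
- Total enrolment needed for 138 three-occasion patients: 138 / (0.9 × (1 − p))

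| p (assumed) | n per arm | Power | Enrolment needed |
|---|---|---|---|
| 20% | 58.3 | 0.73 | 192 |
| 30% | 51.0 | 0.67 | 220 |
| 50% | 36.5 | 0.53 | 307 |

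A second calculation starts from 138 in total, without the reserve, and uses a noncentral F with 2 numerator degrees of freedom calibrated to 80%. It gives about 70%, 64% and 48% for the same shares.

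Break-even: 162 × 0.9 = 145.8 and 1 − 138 / 145.8 = 0.053. With 10% dropout, an early-discharge share above about 5% takes the three-occasion set below 138.

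**4. Can timing distort the comparison?**

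A simulation with invented inputs checks whether it is possible. Baseline scores have mean 0 and SD 2. Weekly gain has mean 1 and SD 0.5, with 0.2 added in the intervention arm. Discharge comes when the score reaches 10, not before week 2. Early discharge is then 33% in control and 47% in intervention.

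| Comparison | Group difference |
|---|---|
| True value at 8 weeks | 1.58 |
| Discharge score in the 8-week cell | 0.95 |
| Early leavers deleted | 0.65 |
| At discharge | 0.00 |

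In this set-up both routes shrink the difference. The sizes, and the direction too, follow from the assumed discharge rule and are not estimates for this trial.

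**The case against.** The strongest reply is that much here is unknown. The article gives neither the early-discharge share, nor length of stay by arm, nor the rule for entering early leavers' data. Handling of deaths and dropouts commonly sits in an analysis plan. The sample size already allows for dropout, and the Discussion admits "the high rate of drop-out due to illness or death of this frail patient group" and short exposure before discharge. All of that stands, and the point does not rest on how deaths or dropouts are handled. It rests on the Procedure rule and the named model not fitting together. A simple before-and-after comparison could take every patient under the Procedure rule, but the Data-analysis section does not specify one.

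Several stronger readings are tempting, and the document does not support them:

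- A reader might infer that recovery sets the time of both follow-up occasions. The 8-week occasion is fixed for those who stay, and discharge also depends on personal situation.
- A reader might infer that the best recoverers and the sickest patients are the ones lost. Nothing in the article shows who leaves early.
- A reader might take the power loss as certain. It applies only if early leavers are deleted. If the discharge score fills the gap, no patient is lost and the fault is one of timing.
- A reader might put a number on the bias, for instance 0.05 SD of recovery per week × 2 weeks' difference in stay = 0.10 SD, one third of the planned 0.30. Neither input comes from the article.
- A reader might conclude that the result is biased. It can be, if length of stay differs between arms, and that is not established.

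Analysing the Barthel Index at three moments is not an error, although it is scored weekly.

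**Conclusion.** The point holds in limited form. The Procedure rule gives patients discharged before 8 weeks two distinct occasions, while the Data-analysis and Sample size sections require three. Following the article as written means deleting these patients or placing a score where it does not belong. The discharge occasion, where the primary goal lies, also falls at unequal times that depend partly on the patient's condition.

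The power loss is conditional on deletion, on the assumed early-discharge shares, on 10% dropout and on the claimed 80% at 69 per arm, which could not be confirmed. Timing bias is possible in either route, but its size cannot be derived from the document.

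**What to change.** Replace the repeated-measures MANOVA with a linear mixed model for each outcome:

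- use the actual time of each assessment since baseline;
- enter each assessment once, at its own time, and never copy a discharge score into the 8-week cell;
- keep patients who have only two occasions;
- report length of stay by arm beside the results.

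State openly whether the main contrast is at discharge, which is the goal in the Background, or at 8 weeks. Choosing 8 weeks changes that goal and should be declared as such; the 8-week values of early leavers would then be model-based. Keeping discharge means comparing patients at unequal times, so the result must be read with length of stay. Using all weekly Barthel scores in the same model is optional.

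The cost is mainly analysis wording, provided that assessment dates are recorded; the article does not say so and this must be confirmed. The model assumes a shape for recovery over time and that missing values are missing at random given what was observed. It does not remove differences between nursing homes that coincide with arm.
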